### Sampling and randomization procedures

Eligible schools are public-sector government secondary schools located in Sofala Province, Mozambique and with a < 30-min drive from an emergency department with co-located government psychiatric/mental health services. These 21 target schools had a total of 16,432 students enrolled in normal daytime classes of 10th grade in 2024 (Table 2). We will randomly allocate the 21 schools 1:1:1 to the three arms using constrained randomization to balance school size (number of total students enrolled in 10th grade in 2024) and rural/peri-urban/urban location. In previous work among youth in schools in Mozambique we had approximately 90% of enrolled students return parental consent forms and participate [13]. Randomization will be done using the cvcrand command in Stata. Thus, we anticipate screening approximately 14,788 students for active sucidal ideation in this trial. Based on pilot data [13] we estimate approximately 14% of those screened to express active suicidal ideation. Recruitment will progress until 2,100 youth are recruited and enrolled in the study across arms. If needed to achieve target recruitment, we will recruit additional students balanced across arms attending 9th or 11th grades.

### Primary statistical analyses

Individual-level primary and secondary outcome data will be analyzed using generalized linear mixed models using the binomial family, logit link, and random effects at the school and individual level. Primary analyses will compute odds ratios for suicidal behavior in the past month comparing the SPI alone and the TCBT-S arms to EUC; primary outcome analyses will be done at 6 months post intake. We will also conduct supplementary analyses of primary and secondary outcomes at 3 months post intake. Sensitivity analyses will utilize gaussian models to directly compute differences in the proportion of SPI and TCBT-S with suicidal behavior compared to EUC. Student (age, sex, grade) and school (size, location) will be considered for inclusion based on balance. Secondary analyses will utilize the same modeling approaches to evaluate odds ratios for suicidal ideation and PHQ-9 ≥ 10 as well as directly comparing outcomes between SPI alone and TCBT-S arms. We will also examine absolute differences in PHQ-9-MZ scores across groups using gaussian models. Sex as a biological variable will be assessed using pre-specified interaction sub-analyses to examine differential SPI and TCBT-S effects for females vs. males. For the RE-AIM maintenance domain, we will repeat all analyses at 12 and 24 months. All statistical analyses will be conducted blinded to study arm.

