### Primary study power assessment

A 2021 meta-analysis of 6 studies of suicide safety planning interventions in high-income contexts found a global relative decrease in SB of 43% (RR: 0.57; 95% CI: 0.41–0.79). Using a conservative alpha value of 0.025 to account for multiple comparisons in the 3-arm cRCT design, an ICC of 0.02, estimated average cluster size of 100 students expressing active SI (14% of 14,788 students screened), we will have > 80% power for a conservative relative decrease in SB of 35%. This represents an absolute difference of 13%, with an estimated 37% of control students with SB in the past month compared to 24% in the intervention groups. See Table 4 for power under varying effect estimates and mean number of students with active SI. Currently there is no consensus in the statistical literature on whether three-arm cRCTs should adjust their alpha value for multiple comparisons with a concurrent control group; half of published trials have adjusted for multiple comparisons and half have not adjusted [50, 51]. Since our two arms are testing a related treatment (SPI alone versus TCBT-S) we argue that more stringent control of family-wise error rate should be employed. Thus, we have chosen to use the conservative Bonferroni correction to account for multiple comparisons in our primary outcome assessment (Alpha = 0.05/N primary outcome tests = 0.025). If we employ an alpha of 0.05, we will have > 80% power to detect a relative decrease of 32.5% (an absolute difference of 12%).

**Table 4 Tab4:** Power under various conditions. Green indicates power > 80%

Mean number of students with active SI per school						
**Primary Outcome:** Decrease in Suicidal behavior in past month from 37% (p1-p0)		60	80	100	120	140
	12.5%	.67	.72	.76	.79	.81
	15%	.84	.89	.92	.93	.94
	17.5%	.95	.97	.98	.99	.99
	20%	.98	>.99	>.99	>.99	>.99

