### SPI/TCBT-S mechanisms assessment approach

Building on existing published theoretical models of SPI and TCBT-S [30, 59], ongoing studies examining mechanisms of effects [60–62], as well as recent reviews [63] proposing mechanisms of action for SPI and cognitive behavioral interventions for suicide prevention [64] we have specified an intervention-mechanism-outcome conceptual model including six hypothesized mechanisms of action for effects of SPI alone and TCBT-S (see Fig. 5). Utilizing mechanism outcome data collected at intake and longitudinally we will test effects of hypothesized mechanisms and moderators using longitudinal structural equation modeling. Hypothesized mechanisms, preconditions, and moderators will be collected at intake and each effectiveness outcome measurement (3, 6, 12, and 24 months). Table 6 summarizes use of validated measurement approaches [65–70] (where available) to be used for each mechanism. To facilitate feasibility of measurement across numerous mechanisms scales, our team adapted questions from otherwise validated measures (Table 6), selecting questions with high factor loadings from applicable constructs. Primary analyses of mechanisms will occur at the end of the primary effectiveness outcome (6 months). Secondary analyses will occur at the end of the maintenance phase (24 months).

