***Moderators***	
Patient engagement	Study Visit Reports
Sex	Study Enrollment Form
Age	Study Enrollment Form
Baseline Suicide Risk	Columbia Suicide Severity Rating Scale (C-SSRS)
Depressive Symptoms	Patient Health Questionnaire (PHQ-9-MZ)

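### The primary model admits school size and location only on observed balance, although the randomisation is constrained on these two factors; the rule tends to drop them and makes the test conservative if they are prognostic

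*Protocol article*

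**What the plan says.** Under Sampling and randomization procedures: "We will randomly allocate the 21 schools 1:1:1 to the three arms", by "constrained randomization to balance school size (number of total students enrolled in 10th grade in 2024) and rural/peri-urban/urban location".

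Under Primary statistical analyses, the outcome model is one of "generalized linear mixed models using the binomial family, logit link, and random effects at the school and individual level". Covariates are governed by one sentence: "Student (age, sex, grade) and school (size, location) will be considered for inclusion based on balance". It gives no balance measure or threshold. The same section says that the analyses are done blind to study arm.

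Table 6 lists "Baseline Suicide Risk", measured with the C-SSRS, as a moderator for the exploratory mechanism model. The mechanisms section states: "Hypothesized mechanisms, preconditions, and moderators will be collected at intake and each effectiveness outcome measurement (3, 6, 12, and 24 months". The C-SSRS also defines the primary outcome. Its intake value is not a candidate covariate for the primary model, and neither is the intake PHQ-9-MZ for the depressive outcomes.

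**The concern.** The two sections work against each other. Constraining the allocation on size and location makes the arms alike on both, so the variation between arms due to these factors is largely gone. The analysis gets the benefit only if it also takes them out of the error variance. A rule that looks at balance will usually find none lacking and leave both out. The school random effect then absorbs their variance, and the standard error of the arm comparison is larger than the design warrants.

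Balance is also the wrong criterion for age, sex and grade. Precision depends on how well a covariate predicts the outcome, not on whether it happens to differ between arms. Without a stated threshold, the covariate set of the primary model is settled only once data are in hand.

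Baseline suicidal behaviour matters for a different reason. Schools are randomised before students are screened and enrolled by workers trained for their arm, so severity at intake could differ between arms. The candidate list has no measure of severity.

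**Working it through.** **Inputs from the protocol (Primary study power assessment).** 37% against 24%; ICC 0.02; 100 students per school; 7 schools per arm; alpha from "Using a conservative alpha value of 0.025 to account for multiple comparisons in the 3-arm cRCT design". Sidedness is not stated; two-sided is assumed.

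**1. The plan's own figure.** Design effect 1 + 99 × 0.02 = 2.98. Effective n per arm 700/2.98 = 234.9. Variance sum 0.37 × 0.63 + 0.24 × 0.76 = 0.4155. SE = √(0.4155/234.9) = 0.0421. Ratio 0.13/0.0421 = 3.09. Normal-approximation power Φ(3.09 − 2.241) = 0.80 (0.802 unpooled, 0.796 pooled). Table 4 at 100 per school gives 0.765, 0.915, 0.980 and 0.997, and every cell of the table is matched within 0.02. The plan's figure takes no credit for covariates.

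**2. Where the variance lies.** A school mean has relative variance 0.02 + 0.98/100 = 0.0298, of which 0.02/0.0298 = 67% is between schools.

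**3. Effect of adjustment.** Let R² be the share of between-school variance explained by size and location, and r the correlation of baseline behaviour with the outcome. The documents give neither, so both are assumed, with r = 0.3.

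- w = 0.02(1 − R²) + 0.0098(1 − r²)
- SE = √(0.4155 × w/7), λ = 0.13/SE
- Power from the noncentral t with noncentrality λ, two-sided alpha 0.025

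Size costs 1 school-level degree of freedom and location 2. Two references are shown: two arms only (12 df, falling to 9) and all three arms in one model (18 df, falling to 15).

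| Model | w | λ | Two-arm t | Three-arm t |
|---|---|---|---|---|
| Unadjusted | 0.0298 | 3.09 | 0.70 (12 df) | 0.74 (18 df) |
| Adjusted, R² = 0 | 0.0289 | 3.14 | 0.67 (9 df) | 0.74 (15 df) |
| Adjusted, R² = 0.10 | 0.0269 | 3.25 | 0.71 | 0.77 |
| Adjusted, R² = 0.25 | 0.0239 | 3.45 | 0.76 | 0.82 |
| Adjusted, R² = 0.50 | 0.0189 | 3.88 | 0.86 | 0.90 |

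Baseline behaviour alone (R² = 0, no school-level df spent) moves the two-arm figure from 0.699 to 0.713. Design factors alone at 9 df give 0.660 at R² = 0 and 0.693 at R² = 0.10, both below 0.699.

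**4. Effect of the balance rule under constrained randomisation.** School means were simulated on the Table 2 schools, keeping the best-balanced 10% of sampled allocations and entering a factor only if its balance test gave p < 0.10. Both settings are assumptions. The rule left out size and location in all sampled allocations. Nominal alpha is 0.025.

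| R² | Type I error: balance rule | Type I error: always adjusted | Power: balance rule | Power: always adjusted |
|---|---|---|---|---|
| 0 | 0.024 | 0.024 | 0.719 | 0.682 |
| 0.3 | 0.014 | 0.028 | 0.725 | 0.782 |
| 0.6 | 0.005 | 0.026 | 0.742 | 0.898 |

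With prognostic factors, the balance rule gives a test well below its nominal level and loses about 6 points of power (R² = 0.3) to 16 points (R² = 0.6). With non-prognostic factors, always adjusting loses about 4 points.

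**The case against.** Several objections have weight.

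- **The error is on the safe side.** The test is conservative, so a reader who infers that a positive result would be unsound goes too far. This stands; the harm is lost power.
- **Adjustment can cost power.** If size and location explain little, the three degrees of freedom are not repaid. This stands, and the tables show it.
- **Discretion is limited.** The candidate list is short and stated in advance, and analysis is blind to arm. A reader might infer that analysts could steer the result; the documents do not support that. Blinding does not fix which covariates enter, however, and no criterion is given.
- **The wording is soft, and the threshold may be in the analysis plan.** The sentence speaks of considering covariates, not of excluding every balanced one. The missing threshold alone would be no finding. The point rests on the stated criterion, which conflicts with the stated design whatever threshold is used.
- **Baseline may enter by another route.** The individual random effect could indicate a repeated-measures model that includes intake. The article does not say so.
- **The simulation is a simplification.** It analyses school means, not the planned mixed model, and its constraint and balance threshold are assumed. It supports the direction better than the exact size.

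**Conclusion.** The point holds as a badly chosen rule that should be changed. The direction is clear: after constrained randomisation on size and location, choosing covariates by balance tends to omit those two, and the test is conservative when they are prognostic. The size is uncertain. It runs from a small loss through adjusting, if the factors explain nothing, to a gain of about 0.16 in power if they explain half of the between-school variance (0.70 to 0.86 two-arm, 0.74 to 0.90 three-arm, with r = 0.3).

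Three stronger readings are not supported. First, the 0.70 or 0.74 does not show that covariate handling breaks the stated power above 80%. That figure reproduces at about 0.80, and the drop comes from using a t reference for few schools instead of the normal approximation, which is a separate matter. Second, leaving out baseline behaviour does not cost much precision: about 0.01 in power at r = 0.3. Its main value is protection against severity differences arising from enrolment after randomisation. Third, nothing in the documents shows that baseline behaviour is the strongest available predictor, and all enrolled students already report active ideation.

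**What to change.** Replace the covariate sentence with wording such as: *All primary and secondary models adjust, regardless of observed balance, for the constrained-randomisation factors (10th-grade enrolment; urban, peri-urban or rural location), baseline past-month suicidal behaviour on the C-SSRS, age and sex. Models for depressive outcomes also adjust for baseline PHQ-9-MZ. Unadjusted models are reported as a sensitivity analysis.*

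Make the change before outcome data are seen. It needs a wording change only, since the C-SSRS and PHQ-9-MZ are already taken at intake. The costs are about three school-level degrees of freedom, a small power loss if size and location turn out not to be prognostic, and an odds ratio that is conditional on the covariates unless it is standardised.

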### Primary study power assessment

A 2021 meta-analysis of 6 studies of suicide safety planning interventions in high-income contexts found a global relative decrease in SB of 43% (RR: 0.57; 95% CI: 0.41–0.79). Using a conservative alpha value of 0.025 to account for multiple comparisons in the 3-arm cRCT design, an ICC of 0.02, estimated average cluster size of 100 students expressing active SI (14% of 14,788 students screened), we will have > 80% power for a conservative relative decrease in SB of 35%. This represents an absolute difference of 13%, with an estimated 37% of control students with SB in the past month compared to 24% in the intervention groups. See Table 4 for power under varying effect estimates and mean number of students with active SI. Currently there is no consensus in the statistical literature on whether three-arm cRCTs should adjust their alpha value for multiple comparisons with a concurrent control group; half of published trials have adjusted for multiple comparisons and half have not adjusted [50, 51]. Since our two arms are testing a related treatment (SPI alone versus TCBT-S) we argue that more stringent control of family-wise error rate should be employed. Thus, we have chosen to use the conservative Bonferroni correction to account for multiple comparisons in our primary outcome assessment (Alpha = 0.05/N primary outcome tests = 0.025). If we employ an alpha of 0.05, we will have > 80% power to detect a relative decrease of 32.5% (an absolute difference of 12%).

**Table 4 Tab4:** Power under various conditions. Green indicates power > 80%

Mean number of students with active SI per school						
**Primary Outcome:** Decrease in Suicidal behavior in past month from 37% (p1-p0)		60	80	100	120	140
	12.5%	.67	.72	.76	.79	.81
	15%	.84	.89	.92	.93	.94
	17.5%	.95	.97	.98	.99	.99
	20%	.98	>.99	>.99	>.99	>.99

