7	Escola Secundária de Marocanhe	864	CS Mascarenhas	Beira	Peri-urban
8	Escola Secundária de Matadouro	1131	CS de Inhamizua	Beira	Peri-urban
9	Escola Secundária de Muchatazina	860	CS da Munhava	Beira	Urban
10	Escola Secundária do Dondo	1105	CS de Dondo	Dondo	Urban
11	Escola Secundária de Mafambisse	926	CS de Mafambisse	Dondo	Rural
12	Escola Secundária de Macharote	840	CS de Dondo	Dondo	Peri-urban
13	Escola Secundária Graça Machel-Dondo	395	CS de Dondo	Dondo	Rural
14	Escola Secundária Filipe Samuel Magaia	305	CS de Mafambisse	Dondo	Rural
15	Escola Secundária de Nhamatanda	729	HR de Nhamatanda	Nhamatanda	Peri-urban
16	Escola Secundária de Lamego	244	HR de Nhamatanda	Nhamatanda	Rural
17	Escola Secundária de Metuchira	445	HR de Nhamatanda	Nhamatanda	Rural
18	Escola Secundária Marcelino Dos Santos	630	HR de Nhamatanda	Nhamatanda	Peri-urban
19	Escola Secundária Mathias Manuel Kaphesse	713	HD de Caia	Caia	Peri-urban
20	Escola Secundária de Inhaminga	542	CS de Inhaminga	Cheringoma	Rural
21	Escola Secundária de Muxúngue	275	HR de Muxúngue	Chibabava	Rural

In the SPI only arm, following previously tested and piloted protocols in Mozambique, non-specialist healthcare workers will participate in a 5-day practical training provided by Mozambican SPI trainers. Following the apprenticeship model [43], SPI providers will role-play suicide screening and SPI protocol implementation in weekly supervision meetings with trainers. Once providers show competence in role-play they will be certified using the Safety Plan Intervention Rating Scale for Mozambique (SPIRS-MZ) [44] where they will have to achieve adequate or better rating on each scale domain. Consistent with expert recommendations on SPI [28, 31], youth will receive follow-up contacts at two and four weeks post intake to assess risk and review their safety plan. Safety plans will also be reviewed during outcome measurements at 3, 6, 12, and 24 months.

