### SPI/TCBT-S mechanisms assessment power

Overall, this study was powered to test the effectiveness of SPI or TCBT-S to decrease odds of suicidal behavior in the past month. Given the lack of previous research on mechanisms for SPI and CBT-based interventions for suicide prevention in the African context, this aim will focus on an exhaustive examination in search of practically- and clinically meaningful mechanism and moderator effect estimates for further examination in subsequent research. The goal of this aim is to contribute to theory building to inform future studies specifically powered to test hypothesized causal pathway models. No confirmatory hypothesis testing driven by p-value inference will be performed, as recommended when conducting exploratory studies by Leon (2011) [71]. However, we will have a sufficient sample size to have stable effect estimates with reasonable precision based on our design including a baseline measurement and 4 follow-up measurements among a minimum of 100 youth across 21 schools (10,500 observations total).

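### The stated power above 80% for a 35% reduction holds only with equal schools, no loss to follow-up and normal critical values; with Table 2 sizes and a small-sample test it is about 60–71%

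*Protocol article*

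**What the plan says.** The section on primary study power sets its inputs out as follows: "Using a conservative alpha value of 0.025 to account for multiple comparisons in the 3-arm cRCT design, an ICC of 0.02". It continues with an "estimated average cluster size of 100 students expressing active SI (14% of 14,788 students screened), we will have > 80% power" for a relative decrease of 35%, which it spells out as 37% in control against 24% under intervention. Table 4 gives power for larger and smaller effects at 60 to 140 students per school. No variation in school size, loss to follow-up or small-sample correction is mentioned.

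Table 2 lists the 21 schools with their grade-10 enrolment. The sampling section fixes the total: "Recruitment will progress until 2,100 youth are recruited and enrolled in the study across arms". If numbers run short, "we will recruit additional students balanced across arms attending 9th or 11th grades". The primary analysis is a logit mixed model with a school random effect, at 6 months after intake.

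The section on power for the mechanisms aim describes five measurements "among a minimum of 100 youth across 21 schools (10,500 observations total").

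**The concern.** With seven schools per arm, power depends mainly on the number of schools and how evenly participants are spread over them. The stated calculation takes the most favourable value on three counts: equal schools, every enrolled youth analysed at 6 months, and a between-school variance treated as known. The article's own Table 2 contradicts the first. Its Reach analyses expect some youth to be lost, which goes against the second. The small number of schools goes against the third.

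The 35% reduction is presented as conservative beside the 43% of the cited meta-analysis. If true power is well below 80%, a real 35% reduction would be missed more often than readers are told, and they would be misled about what a null result means.

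**Working it through.** **Inputs.** From the power section: 37% vs 24%, ICC 0.02, two-sided alpha 0.025, mean 100 per school. From the sampling section: 7 schools per arm, 90% participation, 14% screening positive. From Table 2: the 21 enrolments, which sum to 16,432 (mean 782.5, SD 380.6, CV 380.6/782.5 = 0.486). At 0.9 × 0.14, they yield about 31 (244 enrolled) to 211 (1,674 enrolled) eligible grade-10 youth per school, with 11 of 21 schools below 100. Loss to follow-up is not given; 0–20% is my assumption.

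**Reproducing the stated figure.**
- Design effect = 1 + (100 − 1) × 0.02 = 2.98.
- Effective n per arm = 700/2.98 = 234.9.
- SE = √[(0.37×0.63 + 0.24×0.76)/234.9] = 0.0421.
- Power = Φ(0.13/0.0421 − 2.241) = 0.802. A pooled variance gives 0.796; an exact 35% reduction (24.05%) gives 0.799.

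The same formula gives .67/.73/.765/.79/.81 for the 12.5-point row of Table 4, which prints .67/.72/.76/.79/.81. It also gives 0.81 for the 12-point difference at alpha 0.05. A t reference on 12 degrees of freedom gives .66, not .76, in the 12.5-point, 100-per-school cell. The printed figures therefore rest on equal sizes, normal critical values and no loss.

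**Unequal schools.** Two standard ways:
- CV design effect: 1 + [(1 + 0.486²) × 100 − 1] × 0.02 = 3.45; effective n = 202.8; power 0.736.
- Mixed-model weighting: effective n = 7 × the mean over schools of mᵢ/[1 + (mᵢ − 1) × 0.02], with mᵢ = 100 × enrolment/782.5. This gives 222.5; power 0.778.

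**Few schools.** A two-arm contrast has 14 − 2 = 12 degrees of freedom; one model for three arms has 21 − 3 = 18. The critical values are 2.560 and 2.445. Power comes from the noncentral t with noncentrality 0.13/SE.

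**Loss.** The mean of 100 is multiplied by (1 − loss).

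| School sizes | Loss | Normal | t, 12 df | t, 18 df |
|---|---|---|---|---|
| Equal | 0% | 0.80 | 0.70 | 0.74 |
| Equal | 20% | 0.77 | 0.66 | 0.70 |
| Table 2, CV design effect | 0% | 0.74 | 0.63 | 0.67 |
| Table 2, CV design effect | 10% | 0.72 | 0.61 | 0.65 |
| Table 2, CV design effect | 20% | 0.70 | 0.60 | 0.63 |
| Table 2, mixed-model weighting | 0% | 0.78 | 0.67 | 0.71 |
| Table 2, mixed-model weighting | 10% | 0.76 | 0.65 | 0.69 |
| Table 2, mixed-model weighting | 20% | 0.74 | 0.63 | 0.67 |

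**Check by simulation.** Beta-binomial data on Table 2 sizes, with allocation balanced on size and a 12-df test, gave 0.65–0.67 with no loss and 0.60–0.65 with 10–20% loss. Normal critical values with the between-school variance estimated from the data gave a type I error of 0.045 against the nominal 0.025.

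**Detectable effect at 80% power, Table 2 sizes, t reference, no loss.** From 37% to 21.6% (CV design effect, 12 df; 42% relative) up to 37% to 22.8% (mixed-model weighting, 18 df; 39% relative).

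**Mechanisms section.** 10,500 = 21 × 100 × 5, so nobody is lost at any visit. If recruitment stops at 2,100, at least 100 in each of 21 schools means exactly 100 in every school, and no school quota is stated.

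**The case against.** The stated figure is not a miscalculation: it follows from its inputs, and Table 4 agrees to about one point. The quarrel is with planning assumptions. Much of the rest of the case against also stands:

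- Table 2 by itself does not bring power to 60%. It costs 2–3 points under the planned mixed model, or about 7 under the more conservative CV formula. The lower figures also need a t reference and an assumed loss.
- Twelve degrees of freedom is not established. If all three arms enter one model, 18 is defensible. The article names no reference distribution, and that choice is commonly left to the analysis plan. Normal critical values would keep power at 0.74–0.78 before loss, but at a type I error that undoes the Bonferroni correction the section argues for.
- Table 4 shows smaller schools: from 100 to 80 students, power for 12.5 points falls from .76 to .72. The column is not labelled as loss, but the sensitivity can be seen.
- Covariate adjustment might recover some power. None is credited in the calculation.

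Three stronger readings are tempting and not supported. A reader might infer that recruitment must fall short, because 14% of 14,788 is 2,070 against a target of 2,100; the 9th- and 11th-grade contingency covers that. A reader might infer that 100 per school cannot be reached; the other grades' sizes are not given, so this is not shown. A reader might infer that capping large schools would cure the problem; even fully equal schools give only 0.70–0.74 with a t reference.

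**Conclusion.** The point holds as a matter of undisclosed and optimistic power assumptions. The stated power sits at 0.80 with no reserve, so any one of the three departures takes it below 80%. Size variation, the only one documented in the article itself, gives 0.74–0.78. Adding a t reference gives 0.63–0.71, depending on degrees of freedom and weighting. Adding an assumed 10–20% loss gives about 0.60–0.69. No variant that uses Table 2 sizes reaches 80%. A true 35% reduction would thus be missed roughly three to four times in ten, against the two in ten implied.

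This rests on the protocol's own rates and ICC, enrolment proportional to Table 2, and a loss rate that the article does not give. It does not show the trial to be underpowered for the full 43% reduction of the meta-analysis: there, power is at least 0.83 before loss, even on 12 degrees of freedom with the CV formula.

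**What to change.** Recompute the power sentence and Table 4 with the Table 2 size variation, a t reference with its degrees of freedom stated, and a stated 6-month loss. State the outcome plainly, for example about 60–71% power for the 35% reduction, or 80% power for roughly a 39–42% relative reduction before any loss.

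In the mechanisms section, replace the minimum of 100 youth by an average of about 100 per school, and say that 10,500 observations assumes no loss.

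The cost is wording and a less favourable stated power. Recruitment, randomization, endpoint and analysis model are unchanged.

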**Methods:**

Using a three-arm, parallel, Hybrid Type-1 cluster randomized trial design, we will randomize 7 secondary schools each to Enhanced Usual Care (EUC), SPI alone, and TBCT-S (21 schools total) to evaluate effects on suicidal behaviors (primary) and suicidal ideation/depressive symptoms (secondary). Exploratory structural equation modeling will examine potential mechanisms of intervention effects. Implementation outcomes, barriers, and facilitators to EUC, SPI, and TCBT-S implementation will be assessed using the RE-AIM evaluation and CFIR determinant frameworks. Costs and cost-effectiveness will be evaluated using a Markov model parameterized with cost and trial outcomes data and be applied to projecting budget impact and potential scale-up to provincial and national levels.

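### Headline power and Table 4 use normal critical values with 7 schools per arm: with small-sample inference that holds 5% family-wise error, power is about 70-74%, not above 80%

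*Protocol article*

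**What the plan says.** The trial randomizes 21 schools, 7 to each of three arms (abstract, Methods). The section Primary statistical analyses sets the primary model as "generalized linear mixed models using the binomial family, logit link, and random effects at the school and individual level". It names two primary contrasts: "Primary analyses will compute odds ratios for suicidal behavior in the past month comparing the SPI alone and the TCBT-S arms to EUC". It gives no estimator, test statistic, reference distribution or degrees of freedom.

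The section Primary study power assessment makes error control a design argument: "we argue that more stringent control of family-wise error rate should be employed". It then chooses Bonferroni: "Thus, we have chosen to use the conservative Bonferroni correction to account for multiple comparisons in our primary outcome assessment". Dividing 0.05 between the two contrasts leaves 0.025 for each. The power inputs are introduced by "Using a conservative alpha value of 0.025 to account for multiple comparisons in the 3-arm cRCT design, an ICC of 0.02", followed by an average of 100 students per school and a fall from 37% to 24%, for a stated power above 80%. Table 4 gives .76 for a 12.5-point decrease with 100 students per school.

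**The concern.** Each primary contrast compares 7 schools with 7, so the between-school variance is estimated from few units: 12 degrees of freedom pairwise, 18 if all three arms are pooled. Normal critical values treat that variance as known. Used in a power calculation, they overstate power. Used for the test, they reject too often.

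The stated power and the stated error control therefore pull against each other. A test that holds family-wise error near 5% does not deliver the power in Table 4, and a test that comes near the tabulated power does not hold 5%. The trial is meant to inform scale-up of either intervention, so either shortfall matters.

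A second and separate question is efficiency. Single-step Bonferroni is never more powerful than Holm, which gives the same family-wise control.

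**Working it through.** **Inputs.** From Primary study power assessment: ICC 0.02, 100 students per school, 37% versus 24%, alpha 0.025 per test. From the design: 7 schools per arm. Sidedness is not stated. Two-sided is inferred, because a one-sided 0.025 test would give about 0.84 for the 12.5-point/100 cell, against the stated .76.

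**1. Reproduce the stated power.**
- Design effect: 1 + 99 × 0.02 = 2.98. Effective sample size per arm: 700 / 2.98 = 234.9.
- Standard error: √[(0.37 × 0.63 + 0.24 × 0.76) / 234.9] = 0.0421. Standardized effect: 0.13 / 0.0421 = 3.09.
- Normal critical value for two-sided 0.025: 2.241. Power = Φ(3.09 − 2.241) = 0.802 (0.796 with a pooled variance).
- 12.5-point/100 cell: standardized effect 2.96, power 0.765 (pooled 0.758), stated .76.
- All 20 cells of Table 4 reproduce within 0.02 in this way.

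**2. Same inputs with t critical values (noncentral t).**

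| | Stated | Normal | t, 18 df | t, 12 df |
|---|---|---|---|---|
| Critical value | – | 2.241 | 2.445 | 2.560 |
| 37% vs 24% | >80% | 0.80 | 0.74 | 0.70 |
| 12.5 points, 100 per school | .76 | 0.76 | 0.70 | 0.66 |
| 12 points, alpha 0.05 | >80% | 0.81 | 0.76 | 0.74 |

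The last row uses the critical values for alpha 0.05. Most Table 4 cells no longer match under either t version.

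**3. Family-wise error if the primary test used normal critical values.** There are two contrasts with a shared control (correlation about 0.5) and 18 df for the variance.
- Variance known: 4.6%.
- REML-type variance: per comparison P(|t18| > 2.241) = 0.038; family-wise 6.8%.
- ML-type variance, shrunk by 18/21: per comparison P(|t18| > 2.241 × √(18/21) = 2.075) = 0.053; family-wise 9.3%.

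The logistic mixed model was also simulated (maximum likelihood, 4,500 null trials per scenario, two runs). A cluster-size coefficient of variation (CV) of 0.5 is close to the 0.49 of the Table 2 enrolments.

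| Test at 0.025 | Family-wise error, equal clusters | Family-wise error, size CV 0.5 |
|---|---|---|
| Mixed model, Wald z | 8.1-9.3% | 9.1-10.3% |
| Mixed model, t 18 df | 5.5-6.3% | 6.7-7.5% |
| Mixed model, t 12 df | 4.7-5.2% | 5.5-6.0% |
| School-level t, 18 df | 4.2-4.6% | 4.6-5.2% |

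With both arms at 24% and equal clusters, simulated power per comparison was 0.74-0.77 for the mixed model on 12 df and 0.75-0.77 for the school-level t-test. That is somewhat above the 0.70-0.74 in step 2 but still below 80%.

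**4. Holm against Bonferroni.** Bivariate normal statistics, correlation 0.5, mean 3.09 for an effective arm, critical values 2.241 and 1.960.

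| | Bonferroni | Holm |
|---|---|---|
| Both arms work: per comparison | 0.80 | 0.85 |
| Both arms work: both shown | 0.69 | 0.78 |
| One arm works: that arm | 0.802 | 0.804 |

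The simulated t-based tests gained 10-12 points for showing both effects. The chance of at least one rejection is the same under the two rules.

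**The case against.** A reader might infer that the plan runs its 5% family-wise error at about 9%. The protocol does not support that. It names a model and not a test, and the reference distribution is commonly left to the analysis plan, which is not shown. Table 4 shows how power was approximated, not how p-values will be computed. The 9% belongs to one option, an uncorrected maximum-likelihood Wald z test. The calculations also assumed simple randomization, whereas Sampling and randomization procedures specifies constrained randomization on school size and location. Analysed without those covariates, such an allocation tends to make tests conservative, and the protocol leaves their inclusion to observed balance. All of this stands, and it limits the error-rate statement to a conditional one.

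A reader might also take Bonferroni to be a mistake. It is not: it is valid, openly justified, correctly computed and used in the power calculation. Nor would Holm repair any inflation, since under the global null the two rules have the same family-wise error. Bonferroni also gives simple simultaneous intervals.

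None of this rescues the power figure. It is stated in the protocol, it starts with no margin (0.796-0.802), and it drops below 80% under any of the small-sample tests examined.

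**Conclusion.** The concern holds for the power statement and conditionally for the error rate. The power above 80% and the 5% family-wise error do not hold together on the protocol's own inputs: t inference gives about 4-6% error (mixed model on 12 df, or a school-level t-test) with power of about 70-74%. Uncorrected z inference would restore the nominal power at about 7-9% error under simple randomization, possibly less under the constrained allocation.

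This rests on a two-sided test, ICC 0.02 on the proportion scale, no dropout and no precision gained from covariate adjustment. The power formula further assumes equal school sizes. Holm is an optional gain in efficiency, worth having mainly if both interventions work.

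**What to change.** - **Test.** State that the primary p-values come from small-sample inference: t with between-school degrees of freedom (12 to 18), or a permutation test over the constrained allocation set. With a maximum-likelihood fit, 12 df is the safer end, since 18 df still left 5.5-7.5% family-wise error in simulation. For a permutation test, keep the set of accepted allocations and confirm that it is large enough to reach the 0.025 level.
- **Power.** Restate the headline (about 0.70-0.74), Table 4 with t quantiles (for example about 0.66-0.70 in the 12.5-point/100 cell) and the alpha 0.05 sentence (about 0.74-0.76 for 12 points).
- **Optional improvement.** Replace Bonferroni with Holm: test the smaller p-value against 0.025 and, if it is significant, the other against 0.05.

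**Cost.** Wording and recalculation only, with no added schools, students or data. The price is an openly lower stated power, of which Holm recovers about 5 points per comparison if both arms work. Under Holm, 97.5% intervals no longer map exactly onto the decisions, and the report should say so.
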